### Recruitment

Various strategies of clinical and community recruitment will be conducted. We have been and will continue utilizing our research participant registry, AD-CARE research program, Memory Care Program, Older Adult Outpatient Clinic, and Greater Rochester Practice-Based Research Network. Together, we have access to over 3000 potentially eligible MCI patients. So far, we have successfully recruited over 500 older adults for multiple NIH observational or intervention studies.

### Allocation

Age (60–75 vs. 76–89) will be the factor for stratification. A block-based randomization strategy will be utilized. Co-I ([name]) will create a randomization schedule in REDCap using a random-number generator. Qualified participants will be randomized after completing baseline data collection. The study staff who is not conducting post-intervention assessments will conduct the randomization procedure.

### Blinding

We have built in 4 strategies to ensure blinding: randomization using permuted blocks, all investigators blinded to group assignments (except the biostatistician [name]), all participants blinded to the study aims and reminded as needed not to discuss their experiences with the outcome assessor, and outcome assessors blinded to the study aims, group assignments, and previous test results, and to interact with participants only for data collection [67]. Assessors will not interact with other staff who are not blinded and will participate in separate meetings. Blinding success will be assessed after each data collection: Was group assignment unveiled? Why? For participants whose group assignments are revealed, a different blinded assessor will collect subsequent data. Other strategies include the use of standardized intervention protocol, forms, and reliable and valid variable measures. The analyses will incorporate all design features (e.g., repeated measures within persons, missing data). Unblinding to investigators and study team will only occur when the data analysis of the primary outcomes is completed.

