#### Concomitant care and interventions permitted or prohibited during the trial

We will exclude individuals who are having an experimental pharmacological or non-pharmacological intervention related to cognitive enhancement from enrolling in the study. After enrollment, any participation in such interventions concurrently will be discouraged. If any enrolled participants choose a concurrent experimental intervention, we will record the type of intervention. Any health care as usual will be permitted. The study is regularly recording and updating the type of care and experimental intervention, if any, from the participants, which may be addressed as covariates in later analyses.

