**Fig. 1 Fig1:**
[figure not shown]
ACT task paradigm. Note. Letter stimuli will be auditorily instead of visually provided

*Electrocardiography (ECG) data* will be collected during rest and ACT task (both inside MRI) using PrismaFit MRI compatible ECG. Three disposable ECG electrodes will be placed in a lead-II configuration to record the ECG signal. A strain gauge will be secured around the lower chest to record respiration rate, and a pulse oximeter will be applied to the index finger to record pulse rate, which will both be considered as potential covariates in analyses using HRV. ECG signals will be conditioned and collected (1000 Hz sampling; 5 Hz for strain gauge) through an integrated A/D board and written to disk and later scored (with BIOPAC MRI compatible ECG processing software). The signals will be collected continuously during the BOLD imaging sequence. High-frequency heart rate variability (HF-HRV) data will be preprocessed with BIOPAC, using methods described previously [37]. Briefly, consecutive R-R intervals will be preprocessed using a filter at 0.12–0.40Hz for generating HF-HRV, and natural log transformation will be applied. We will process 30–60-s segments [to be consistent with BOLD dynamic functional connectivity (FC) analysis time window size] and remove ectopic beats and artifacts by consistent visual inspection between two raters. The first and last four segments, as well as incomplete segments (i.e., <15 s), of each recording at rest and task will be excluded from the analysis. Null values from motion and arrhythmic artifacts in the remaining data will be excluded by dividing the number of null-absent segments by the total number of segments to obtain the percentage of usable data for each participant. A threshold at 70% will be applied to determine subjects with valid rest and task data.

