### Data collection method

Data collectors will have checklists to follow for the data collection visit protocol (e.g., consent obtained, date, participant code, etc.). This checklist will be then reviewed by the Project Coordinator who will monitor for deviations from the protocol. The Project Coordinator will check the first 3 enrollment and consent visit checklists of each data collector. Thereafter, he/she will randomly select 15% of the checklists every data collection cycle (6 months). The project coordinator will generate reports for the PIs to review every data collection cycle. Data collected will be kept in a master data set maintained by the project coordinator. Queries and reports will be run periodically over the course of the study related to the integrity of the data, outliers, missing data, etc. The project coordinator will generate a report after each data collection cycle (every 6 months) that will be discussed with the PIs and project statistician. Any necessary systems change will be evaluated at each of these meetings.

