### Data analysis

#### Determine the intervention effect on outcomes

All primary analyses will follow *the intention-to-treat principle* (e.g., group assignment in the analysis will be based on randomized group assignment regardless of the level of adherence to provide unbiased comparisons of the effects among the groups). This principle will account for any potential data loss. We will fit linear mixed-effect models for each outcome measure, accounting for repeated measures at baseline, post-intervention, and 6- and 12-month follow-up. The models will include fixed effects for data collection visit (categorical variable), group assignment (compare the combined group with other groups), visit and group interaction, respective baseline outcome measure, and covariates identified as being imbalanced among groups. Stepwise variable selection using Akaike Information Criteria will be used to select the fixed effects for inclusion. A random participant-specific effect will be included to account for correlation between visits in the same participant. The model-based average within-group change in outcome measure for each group will be computed at each post-intervention and follow-up point. This will allow us to rank the groups in terms of average within-person gains in each outcome measure. In addition, *the effect sizes of RFB+VSOP and IR+VSOP control for each outcome measure* will also be calculated using standardized mean difference with 95% CI [(*M*_int_ − *M*_control_ at later time) − (*M*_int_ − *M*
_control_ at baseline)]/intra-participant standard deviation; “int” refers to combined intervention or VSOP; “control” here refers to attention control. The effect size of RFB+VSOP will be compared with that of the IR+VSOP control group to determine the additive effect.

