## Data Availability

We will create a database for hosting all data at the University of Rochester (UR) and managed and stored by the UR Information Analyst on-site. A final complete database will be created to host all data which will be stripped of any identifiers and stored pursuant to UR Institutional Review Board protocols. After data entry, cleaning, and linkage, the Information Analyst will provide the research team a de-identified data set for purposes of analysis and manuscript preparation. We will make the data and associated documentation available to users only under a data-sharing agreement as suggested by the NIH that provides for (1) a commitment to using the data only for research purposes and not to identify any individual participant, (2) a commitment to securing the data using appropriate computer technology, and (3) a commitment to destroying or returning the data after analyses are completed. The richness of the data, combined with the interdisciplinary nature of the research team, provides opportunities for future wide disseminations. The interdisciplinary team has a strong history of presenting at local, state, and national conferences that span the fields of neuroscience, gerontology, cognition, and psychophysiology. It is of the utmost importance to this team that the work products from this study will be disseminated in a manner that provides implementation in the field.

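### The biostatistician is exempt from blinding while the primary model's covariates and fixed effects are chosen from the data, and investigators may be unblinded before the conversion judgements are final.

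*Protocol article*

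**What the plan says.** The Blinding section has "all investigators blinded to group assignments (except the biostatistician" as the one stated exception. On timing it adds: "Unblinding to investigators and study team will only occur when the data analysis of the primary outcomes is completed".

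The section on determining the intervention effect lists the fixed effects of the mixed model: visit, group, their interaction, the baseline value of the outcome, and "covariates identified as being imbalanced among groups". It continues: "Stepwise variable selection using Akaike Information Criteria will be used to select the fixed effects for inclusion". It gives no list of candidate covariates and no threshold for imbalance. It names no term that must stay in the model and does not say that selection is done on masked data.

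Other sections add optional covariates. Concurrent care and experimental interventions are recorded, "which may be addressed as covariates in later analyses" (concomitant care section). Respiration and pulse rate are measured, "which will both be considered as potential covariates in analyses using HRV" (ANS flexibility, under Measures).

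Also under Measures, a diagnosis of AD conversion is agreed by the principal investigators and co-investigators. Reversion to normal cognition is handled in a similar way, and each participant receives a final classification at 12 months.

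**The concern.** Choosing a model from the data and knowing the arms can each be acceptable alone. Together they let the person choosing among defensible covariate sets see which set favours which arm. The final report would show one model, and the choice behind it could not be reconstructed. At stake is the error rate of the two comparisons set at alpha 0.025.

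The second gap concerns a judged outcome. The unblinding trigger refers only to the primary outcomes. Conversion and reversion are consensus judgements made by the investigators whom that trigger unblinds, and no text requires the judgements to be final first.

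**Working it through.** **Text.** Three statements are set side by side.

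1. The biostatistician is not blinded. Everyone else among the investigators stays blind until the primary analysis is done, so that analysis is carried out before general unblinding. No analyst is named, but the biostatistician is the one investigator left unblinded.
2. Imbalance among groups cannot be judged without at least coded groups. The selection sentence refers to the fixed effects as a whole. Read literally, it covers group and visit-by-group, which carry the treatment comparison.
3. No masked group codes are mentioned.

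**Size.** The plan gives no figure to reproduce, so the effect was illustrated by simulation.

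Inputs from the Sample size section: alpha 0.025, and 96 evaluable participants in three arms, so 96/3 = 32 per arm. Assumed, because the protocol lists no candidates: K = 3 or 5 covariates, each correlated r = 0.20 or 0.35 with the outcome.

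Data under no treatment effect: y = r(C1 + ... + CK) + √(1 − K·r²)·e, with independent standard normal C and e. Model: y on group plus a covariate subset S, with a t test on group. Four ways of choosing S were compared, with 3000 null trials per setting:

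- Pre-set: no covariates.
- Imbalance rule: covariates differing between arms at p < 0.05.
- AIC: the subset minimising n·ln(RSS/n) + 2p, group always kept.
- Free choice: the subset giving the smallest group p-value, among 2³ = 8 or 2⁵ = 32 subsets.

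| K, r | Variance explained, K·r² | Pre-set | Imbalance rule | AIC | Free choice |
|---|---|---|---|---|---|
| 3, 0.20 | 0.12 | 0.027 | 0.024 | 0.028 | 0.044 |
| 3, 0.35 | 0.37 | 0.021 | 0.016 | 0.021 | 0.059 |
| 5, 0.20 | 0.20 | 0.026 | 0.022 | 0.034 | 0.069 |
| 5, 0.35 | 0.61 | 0.030 | 0.020 | 0.027 | 0.132 |

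The Monte Carlo standard error at nominal is √(0.025 × 0.975/3000) ≈ 0.003. The mechanical rules stay near 0.025. The one AIC value of 0.034 is about three standard errors above nominal, so it may be a small real excess. Free choice gives 0.044/0.025 ≈ 1.8 times to 0.132/0.025 ≈ 5 times nominal. The top value needs covariates that explain 61% of the outcome variance.

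**Conversion.** With 38 randomised per arm, each participant classified differently moves an arm's rate by 1/38 = 2.6 percentage points. The protocol gives no basis for saying how many cases would be borderline.

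**The case against.** An unblinded statistician is not an error in itself, and AIC is an algorithm that leaves little to opinion once its candidates are fixed. Both points stand. The simulation agrees that the written rules, followed mechanically, do little harm. What remains open is the candidate set and the imbalance criterion. An analysis plan that is not shown may settle these. Even so, selection from the data is the method that the protocol itself commits to, so this is more than a detail left to another document.

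On conversion, it is fair to say that diagnostic criteria are stated. The primary models also use 12-month data, so early unblinding is a possibility rather than a plan. The trigger still does not require the classification to be final.

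A reader might infer more than the text supports:

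- That outlier handling is settled by someone who knows the arms. The Data collection method section mentions outliers only as an item in data-integrity queries and reports.
- That the six-monthly report, "that will be discussed with the PIs and project statistician", passes arm information to the principal investigators. Nothing says the reports are by arm, and system changes are only to be evaluated at those meetings.
- That ECG or scan exclusions are open to the biostatistician. ECG artefacts are screened by two raters, with a fixed 70% cut-off for usable data. No role in scan exclusions is given to the biostatistician.
- That the biostatistician knows the arms from the start. The exception carries no date.

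**Conclusion.** The point holds in limited form. The protocol combines an unblinded biostatistician with a primary model chosen from the data, with no forced terms and no masking stated. That this person chooses the model is the natural reading but is not written.

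The 4% to 13% illustrates deliberate choice of the most favourable model. It should not be read as the trial's expected error rate. It rests on assumed covariate numbers and correlations, a single two-arm comparison at one time point in place of the mixed model, and a best-subset search in place of stepwise selection. It is not an upper bound, since more or stronger covariates would raise it. The simulation also always kept the group term, which the plan does not promise.

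The unblinding trigger is a separate, smaller gap, and its effect cannot be quantified from the document. Both gaps merit correction because the change is cheap.

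**What to change.** 1. In the analysis section, replace the imbalance rule and stepwise AIC with a model signed off before the analyst knows arm. Force visit, group, visit-by-group and the baseline outcome. Either name the prognostic covariates in advance, or select them on a file without arm, using only their relation to the outcome. The imbalance rule has to go, because it cannot be applied to such a file. Arm is merged in after sign-off by the Information Analyst, who already has a suitable role: "the Information Analyst will provide the research team a de-identified data set for purposes of analysis and manuscript preparation". If the biostatistician needs the allocation earlier for other duties, naming the covariates in advance is the safer option.

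2. In the Blinding section, set the unblinding trigger to the point when all outcome data, including AD conversion and reversion classification, are locked and the primary analysis is complete.

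This costs changes of wording in the protocol and any analysis plan, slightly later unblinding, and one extra data-handling step. No new staff or data are needed.

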### Data collection method

Data collectors will have checklists to follow for the data collection visit protocol (e.g., consent obtained, date, participant code, etc.). This checklist will be then reviewed by the Project Coordinator who will monitor for deviations from the protocol. The Project Coordinator will check the first 3 enrollment and consent visit checklists of each data collector. Thereafter, he/she will randomly select 15% of the checklists every data collection cycle (6 months). The project coordinator will generate reports for the PIs to review every data collection cycle. Data collected will be kept in a master data set maintained by the project coordinator. Queries and reports will be run periodically over the course of the study related to the integrity of the data, outliers, missing data, etc. The project coordinator will generate a report after each data collection cycle (every 6 months) that will be discussed with the PIs and project statistician. Any necessary systems change will be evaluated at each of these meetings.

### Data management method

Names and other personal identifying information will be confidential. Rigorous procedures will be in place to safeguard and eventually destroy identifiable information to protect the identity of participants. We will keep data collected from participants, written informed consents, and participant contact information in locked filing cabinets in restricted-access office spaces. Data from questionnaires will be identified only by study ID. Electronic datasets will be stored only on a password-protected server within the University. Databases will be housed on secure UR servers. The servers are in a physically secure location and are backed up nightly, with the backups stored in accordance with the retention schedule of daily, weekly, and monthly tapes retained for 1 month, 3 months, and 6 months, respectively. Weekly backup tapes are stored offsite. Computers will be safeguarded from theft and damage (e.g., locks on physical access, virus protection and encryption programs), and no data will be stored in a portable computer. Project files and databases associated with the study will only be available to research personnel through the authorization of the PIs. In addition, study reports (such as aggregated data in progress reports) generated by the research team will provide total anonymity because no names or identifying information will be part of such reports. Participants and staff will be apprised of their rights and responsibilities under the Privacy Act of 1974, including penalties for violations. All staff involved with the research project will receive training on their function, roles, and responsibilities to protect and maintain the privacy and confidentiality of research participants, and will complete NIH-approved training in this area.

Any amendment versions of IRB documents will be kept. Blinding related to randomization is kept in a password-protected file in our server with selected unblinded staff having access. Project files and databases associated with the study will only be available to research personnel through the authorization of the PIs. The UR servers are backed up nightly, with the backups stored in accordance with the retention schedule of daily, weekly, and monthly tapes retained for 1 month, 3 months, and 6 months, respectively. Weekly backup tapes are stored offsite.

Measures for use in the study were selected carefully based on their established psychometric properties for questionnaires, and standardized protocols will be used for measuring brain imaging, blood, and ECG data. All measures will be administered by study staff, Center for Advanced Brain Imaging and Neurophysiology (brain imaging) and Clinical Research Center (CRC, blood) staff, respectively. Data collection procedures will be standardized based on a detailed protocol, and data collectors will be trained to ensure consistency in the procedure. Twice a year, the team will review procedures with all the staff involved in data collection to prevent deviations from the protocols. Finally, all data will be entered into REDCap or a statistical database. The data collection process will entail site staff entering data both directly into databases, using source worksheets (e.g., chart abstract data entered onto data collection source worksheets), and into REDCap directly. Data will be stored in a password-protected management information system and in SPSS databases, which are maintained on a secure UR server. Once data have been verified against source documents, any data entry errors are corrected and data are moved to an archived file. Data entered are immediately stored in a study database where they are accessible for review by the study team. Our data collection project will rely on a thorough study-specific data dictionary defined in an iterative self-documenting process by all members of the research team. Blood samples will be processed as per protocols in the CRC for storage in preparation for analysis.

Staff members will not be allowed to abstract data, interview a subject, or process data from a subject that they know personally. Identification codes rather than names will be used on the data collection forms. The PIs will assure that survey practices adhere to the provisions of the US privacy act of 1974 with regard to surveys of individuals for the Federal government. The handling of data will be limited to numerical values and statistical summaries. Identifiers linking identification codes with individual names are only available to the PI and study staff who contact participants. Data collection into REDCap is stored on a protected server. Personal computers are logged off at the end of each work day to prevent inadvertent access to the network and data stored on the computer. Data will be stored on a protected server and the access will be limited by a password-protected network subdirectory where sensitive data are stored. Sensitive data will not be sent via email. Blood samples identified by code will be stored in a −80°C freezer in the SON level 2 safety biomolecular lab that has limited access.

### Data monitoring

At a minimum, an independent safety monitor (ISM) will conduct reviews early in year 1 and each year of the project thereafter. The first review will be conducted before the formal start of enrollment, reviewing documents (i.e., protocol and data safety monitoring plan) related to the study. In each of the following meetings, ISM will randomly audit 10% of enrolled cases during the period (i.e., between last and current review meeting); the auditing will include reviewing all assessment, intervention, and data management documents to determine if the procedure is aligned with the IRB protocol. Additional meetings with the study team or additional information from the study team will be provided on the recommendation of the ISM. After each meeting, a summary of recommendations made by the ISM as appropriate and (if applicable) the action plan for response will be submitted to NINR.

The study investigators will submit statistical reports to the ISM 1 week prior to the scheduled review. These reports will include all reported data up to and including 14 days prior to the reporting deadline (except for serious adverse events, which are to be reported within 24 h of an event). For each review at which the study is to be considered or monitored, the PI will present an overall progress statement. This brief statement will contain any IRB-approved protocol modifications, the assurance that the study investigators have considered the study’s progress and that there is/is not evidence of safety issues that should be addressed by the ISM. Data will be presented in a blinded manner during the open sessions of the ISM meetings. Data and discussion are confidential. Participant identities will not be known to the ISM. [name], Director of the Aging Research Office, University of Rochester, is the ISM, approved by the funder.

Of note, the interim analyses and decision to terminate the trial will only be initiated and justified by ISM and approved by the funder.

